## Background

Total Knee Arthroplasty (TKA) is a common and generally effective procedure and most of the operated patients have less pain and higher functional ability after the surgery [1]. However, some patients respond poorly to the surgery and chronic pain following TKA remains a major health burden for many patients [2]. “Poor” outcome following TKA is due mainly to disabling pain and impaired function [3, 4]. Thus, persistent knee pain was reported 12 months after TKA in 16.4% of the patients by Baker et al. who followed 9417 patient’ pain using the Oxford Knee Score (OKS) [3]. Similar pain results were reported by Nilsdotter et al. [5]. Most recently, in a systematic review Beswick and colleagues stated that 20% reported persistent function-limiting pain 6 months or more following a TKA, despite an apparently normally functioning prosthesis [4]. Routinely screening for patients at high risk for persistent pain after the surgery is suboptimal and not common practice [6]. This practice has potential to change because resent research shows that we are able to identify several psychological predictors of poor outcomes after knee arthroplasty. From the literature on non-surgical chronic pain the evidence suggests that pain disability does not result solely from the severity of pain but is largely influenced by patients’ adjustment and interpretation to their pain [7, 8]. Among the most well documented and powerful psychological predictors of poor outcome following TKA is pain catastrophizing [9]. Pain catastrophic thoughts are related to pain rumination, pain magnification and helplessness in the face of pain. New research has shown that patients with these thoughts are at higher risk of having persistent pain and lower physical function after the operation than patients with low levels of pain catastrophizing before TKA [2, 10–14].

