**Fig. 2 Fig2:**
[figure not shown]
Diagram of the patient flow through the study

Randomization will be conducted by permuted blocks and an independent staff will prepare consecutively numbered, sealed envelopes. The physiotherapists and nurses who execute the baseline and follow-up testing will be blinded for the randomization. The patients and the three physiotherapists delivering the pain coping education cannot be blinded.

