### Preoperative screening and selection of “high Pain Catastrophizing” patients

Patients will be screened preoperatively at the outpatient clinic after they are scheduled for a TKA using the questionnaire Pain Catastrophizing Scale (PCS) [27]. PCS consists of 13 questions where the patients rate their thoughts and feelings when they are experiencing pain. The total score is ranging from 0 indicating no “pain catastrophizing” to 52 indicating worst “pain catastrophizing”. Each item are rated on a 5-point scale ranging from “not at all” to “all the time”. The Danish version of PCS is considered valid for use in clinical pain samples and the internal consistency is found acceptable [28].

The cut-off score for PCS is chosen on basis of data collected in the years 2011–2013 at Holstebro Regional Hospital. 530 TKA patients answered the PCS before the operation. Median PCS score was 16 range (0–52). In the present trial we want to include the 33% of our TKA population with the highest PCS score. This means that we will use the 66th percentile of the total score to define the cut-off in this study. Thus, patients with a PCS score on 23 or higher are eligible for inclusion and in this study defined as patients with “high pain catastrophizing”.

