### Sample size and statistical analysis

The primary outcome measure will be VAS under activity measured on a continuous 100 mm scale 12 month after the operation. Clinically important differences between the two groups is detected to be 18 mm [46, 47]. Based on earlier studies we assume a common standard deviation between participants of 19 mm on VAS [2, 10, 48]. With a significance level at 0.05 and the power at 0.90 the study needs 23 patients in each arm. Taking into account a loss to follow-up after 1 year on approximately 20% we aim at including 28 patients in each group a total of 56 patients.

Clinical and demographic characteristics as well as baseline data will be presented to show the baseline comparability of the two groups. Data from the patients who withdraw from the study will also be examined. For each group descriptive statistics will be presented at baseline and three and 12 months postoperative. Normally distributed data are described by means and standard deviation (SD), and data not normally distributed by medians and interquartile range (IQR). The primary analysis will use the intention-to treat principle including all randomised participants. Patients who discontinue the intervention will be encouraged to participate in the follow up test anyway, and those who accept will be included in the analyses according to their original group assignment. The primary outcome pain is measured on a continuous scale and between-group mean differences and 95% confidence intervals from baseline to 3 and 12 months will be analyzed by a mixed effects linear regression model with a random person level and systematic effects of time, group and the interaction between time and group. We will employ multiple imputation methods in order to assess the sensitivity of the mixed model to any informative missing values. Imputations will be performed using baseline characteristics and non-missing pain measurements on individual levels. Secondary outcomes will be analysed as above for normally distributed measures or for binary outcomes, we will use logistic regression with a robust variance estimate to account for the repeated measurements. Standard diagnostic plots will check model assumptions. The statistical analyses will be performed using STATA 13 (StataCorp, College Station, TX) software package. The significance level will be set at 0.05.

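### The continuous screening PCS, complete and taken before randomisation, is left out of the primary model; adding it with a time interaction is a cheap, modest gain in efficiency and not the repair of a bias

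*Protocol article*

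**What the plan says.** All of this is in the protocol article.

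- **Screening score.** The section on preoperative screening has every candidate complete the PCS (0 to 52) at the outpatient clinic, and sets the entry rule: "Thus, patients with a PCS score on 23 or higher are eligible for inclusion". The score is therefore available for everyone randomised.
- **Order of events.** The paragraph on randomisation under Exclusion criteria, and the limitations in the Discussion, place randomisation directly after inclusion and ahead of the baseline assessments. The screening PCS precedes allocation; the baseline PCS of Table 2 follows it.
- **Prognostic standing.** The Background states: "Among the most well documented and powerful psychological predictors of poor outcome following TKA is pain catastrophizing".
- **Allocation.** "Randomization will be conducted by permuted blocks", with no stratification factor named.
- **Primary model.** Between-group differences from baseline to 3 and 12 months come from a "mixed effects linear regression model with a random person level and systematic effects of time, group and the interaction between time and group". No PCS term is listed.
- **Other uses of PCS.** It is a secondary outcome at baseline, 3 and 12 months. Baseline characteristics are to be tabulated and used in the imputation model, without PCS being named.

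**The concern.** The trial selects patients on a score that it regards as strongly prognostic, records that score for everyone before allocation, and then uses the continuous value neither to balance the arms nor to adjust the primary analysis. With 28 patients per arm, a chance difference in entry PCS can move the VAS comparison, and the variation PCS explains stays in the error term.

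The screening score is also a safer covariate than the Table 2 measures. Those are collected after allocation from patients who are not blinded; the screening score cannot have been influenced by the arm. At stake are some precision and a covariate fixed in advance, rather than one chosen after the baseline table has been seen.

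**Working it through.** **Inputs from the article** (Sample size and statistical analysis): target difference 18 mm, between-participant SD 19 mm, alpha 0.05 (taken as two-sided), power 0.90, 28 per arm. **Assumed, because the article gives no values:** within-person VAS correlation ρ = 0.4; in-trial correlations of screening PCS with VAS at baseline (r0) and at 12 months (r12).

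**1. The plan's own figure.** n = 2 × [19 × (1.960 + 1.282) / 18]² = 23.4 per arm. The article has "the power at 0.90 the study needs 23 patients in each arm". Rounding up gives 24, and power at 23 is 0.895, so the figure reproduces to within rounding. It is sized on a level SD: "we assume a common standard deviation between participants of 19 mm on VAS". The model's contrast, however, is change from baseline, so both contrasts are examined.

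**2. PCS as a main effect only, stated contrast.** The 12-month time × group term is the difference between arms in mean change. A patient's screening PCS is constant over visits, so a main effect shifts all visits equally and cancels. In 100 simulated trials (28 per arm, ρ = 0.4, PCS correlation 0.3 at every visit):

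- complete data: largest difference in the estimate 6 × 10⁻¹³ mm; standard error 5.56 with and without PCS;
- 20% missing at 12 months: standard error 5.97 without PCS, 5.96 with it.

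**3. PCS plus PCS × time, stated contrast.**

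- Variance of change = 2 × 19² × (1 − 0.4) = 433.2 mm².
- Slope of change per SD of PCS = 19 × (r12 − r0).
- 95% range of chance PCS imbalance = 1.96 × √(2/28) = 0.524 SD.
- Shift = slope × 0.524. Variance removed = slope² / 433.2.

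| r12, r0 | Slope (mm per SD) | 95% shift (mm) | Variance removed | Fall in SE before cost |
|---|---|---|---|---|
| 0.3, 0 | 5.7 | ±3.0 | 7.5% | 3.8% |
| 0.3, 0.1 | 3.8 | ±2.0 | 3.3% | 1.7% |
| 0.3, 0.3 | 0 | 0 | 0 | 0 |

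Cost of estimating the terms, from the simulation of the last row: 5.61 against 5.56 with complete data (0.9% worse) and 6.03 against 5.97 with 20% missing (1.0% worse). Simulating the first row at 28 per arm leaves a net gain of about 2.8%. At 23 per arm the net effect again runs from about 1% worse to about 3% better.

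**4. 12-month level contrast.** Fall in SE = 1 − √(1 − r²); 95% shift = 1.96 × r × 19 × √(2/28).

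| In-trial r | Fall in SE before cost | 95% shift (mm) |
|---|---|---|
| 0.2 | 2.0% | ±2.0 |
| 0.3 | 4.6% | ±3.0 |
| 0.4 | 8.3% | ±4.0 |

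**5. Which r is plausible.** Only the top third on PCS is enrolled. If PCS were normal, its SD in that third would be u = 0.529 of the full SD, and the in-trial correlation would be r·u / √(1 − r² + r²u²). A full-population r of 0.3 becomes about 0.16 (SE falls 1.4%) and 0.5 becomes about 0.29 (SE falls 4.4%). An in-trial r of 0.3 needs about 0.51 in the full population, and 0.4 needs about 0.64. The upper rows above are therefore generous.

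**The case against.** The case for leaving the model alone is substantial, and most of it stands.

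- **Nothing is stated wrongly.** Randomisation is not stratified by PCS, so no design factor is ignored, and the confidence interval already allows for chance imbalance. A reader might infer that the omission biases the result; it does not.
- **The stated contrast already removes stable differences between patients.** A reader might infer that PCS imbalance passes in full into the primary estimate, or might convert r² into extra patients' worth of information. Both readings belong to a level contrast. In the stated model the effect depends on whether PCS predicts change in VAS, which the article does not show.
- **Prediction above the cut-off is not documented.** The Background contrasts patients who catastrophize with those low on the trait; it does not address gradation from 23 upwards. It does describe prediction of persistent pain after surgery, which makes a stronger correlation at 12 months than at baseline plausible, but no more than that.
- **PCS is not discarded.** A reader might say that it serves only as a pass/fail gate. That describes the screening score, not the instrument, which is a secondary outcome and may be among the baseline characteristics used for imputation.
- **Extension to PCS as an outcome is not supported.** Baseline PCS would be a response in that model, and the screening score would largely predict that row.
- **A covariate list may sit in an analysis plan not shown.** That is possible. Even so, the article does enumerate the primary model's terms, so a suggestion about them addresses something it fixes.

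**Conclusion.** The point holds as a low-severity improvement in efficiency. The continuous screening PCS is complete, precedes allocation and is presented as strongly prognostic, yet it is in neither the allocation scheme described nor the primary model.

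For the contrast the plan estimates, what adjustment would change is small and could have either sign: about 1% loss to 3% gain in standard error, and chance-imbalance shifts of 0 to about 3 mm, at r12 = 0.3 and ρ = 0.4. The larger figures, up to 8% in standard error, apply to a 12-month level contrast at an in-trial r of 0.4, which restriction to the top third makes hard to reach. Every one of these sizes rests on assumed correlations. What does not depend on them is that, with complete data, a PCS main effect alone leaves the change contrast as it is.

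**What to change.** In Sample size and statistical analysis, add one sentence to the primary VAS model, for example: *The model will also include, as fixed covariates, the continuous PCS total recorded at outpatient screening before randomisation and its interaction with time; the baseline PCS of Table 2 will not be used for this purpose.* The interaction with time must be kept, for the reason shown in step 2 of the working. Limit the change to the primary VAS model.

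The cost is that one sentence and a few degrees of freedom. No new data are needed and the covariate has no missing values, because the score is required for entry. The downside is a loss of about 1% in precision if PCS does not predict change in VAS. The change should be made before outcome data are seen.

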
## Methods/Design

### Design

This study is a single centre double-arm parallel group design trial with 1:1 allocation with 1-year follow-up. Measurements will be taken at baseline before the operation and 3 and 12 months after the operation.

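### A random person effect alone ties all three visits to one variance and one correlation, so the standard error of the baseline-to-12-month contrast can be wrong in either direction, more plausibly too small

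*Protocol article*

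**What the plan says.** Under Design, the Protocol article sets three assessments: "Measurements will be taken at baseline before the operation and 3 and 12 months after the operation". Under Sample size and statistical analysis, the endpoint is fixed: "The primary outcome measure will be VAS under activity measured on a continuous 100 mm scale 12 month after the operation". The quantity to be estimated is given as "between-group mean differences and 95% confidence intervals from baseline to 3 and 12 months", obtained from a linear mixed model "with a random person level and systematic effects of time, group and the interaction between time and group".

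That sentence names one random term, the person. The section names no residual covariance, random slope or visit-specific variance. A robust variance is mentioned only for the logistic models of binary outcomes, so it does not clearly cover the continuous primary model. Diagnostic plots are planned, but the section does not say what follows if they show a problem. The only SD is the one used for the sample size: "we assume a common standard deviation between participants of 19 mm on VAS". No correlation between visits is given.

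**The concern.** A random person intercept with ordinary residuals is compound symmetry: the same variance at every visit and the same correlation for every pair of visits. That is doubtful here because the knee replacement falls between the first visit and the other two. The two post-operative scores may well resemble each other more than either resembles the pre-operative score, and the spread of pain scores may differ before surgery, at 3 months and at 12 months.

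The contrast from baseline to 12 months spans both the operation and the longest interval. If its two scores have the lowest correlation, its true variance is above the average that the model applies, and the confidence interval is too short. If the 3-month scores are the noisiest, the average is pulled up and the interval can be too long. In either case the stated 95% coverage and 5% error rate of the main result depend on an assumption for which the plan gives no support.

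**Working it through.** **Inputs from the Protocol article.** Difference 18 mm, SD 19 mm, significance level 0.05 (taken as two-sided), power 0.90, 23 per arm needed, 28 per arm recruited, about 20% loss, three visits.

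**Assumed inputs.** SDs by visit and correlations between visits (none are given), time as three categories, and independent equal-variance residuals beside the person effect.

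**The plan's own figure.** n per arm = 2 × [19 × (1.960 + 1.282)/18]² = 23.4, against 23 stated. Power at 23 per arm is 0.895 by the normal approximation. The figure reproduces to within rounding. It is a two-group comparison at one time point, so the covariance structure does not enter it.

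**Formulas, complete data, n per arm.** Write D(a,b) = SDa² + SDb² − 2·r(a,b)·SDa·SDb for the variance of the difference between two visits.

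- True: SE² = (2/n) × D(0,12).
- Random-intercept model: SE² = (2/n) × [D(0,3) + D(0,12) + D(3,12)]/3. The model variance of a change is twice the residual variance, and the residual variance estimates mean variance minus mean covariance.
- Type I error of a nominal 5% test ≈ 2 × [1 − Φ(1.96 × SE model/SE true)].

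**Worked case.** SD 19 at all visits, correlations 0.3/0.2/0.6 (0-3, 0-12, 3-12 months), n = 23:

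- D(0,3) = 722 × 0.7 = 505.4; D(0,12) = 722 × 0.8 = 577.6; D(3,12) = 722 × 0.4 = 288.8; average 457.3.
- True SE = √(2 × 577.6/23) = 7.09 mm; model SE = √(2 × 457.3/23) = 6.31 mm; ratio 0.890.
- Type I error = 2 × [1 − Φ(1.744)] = 8.1%.

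**Counter-case.** SD 19/24/19, correlations 0.3/0.3/0.6:

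- D(0,3) = 663.4; D(0,12) = 505.4; D(3,12) = 389.8; average 519.5.
- Ratio = √(519.5/505.4) = 1.014; type I error about 4.7%.

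**Range** (n = 23 per arm; simulated column from 20,000 trials with a normal critical value):

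| SD 0/3/12 | r 0-3/0-12/3-12 | True SE | Model SE | Ratio | Type I, formula | Type I, simulated |
|---|---|---|---|---|---|---|
| 19/19/19 | 0.5/0.5/0.5 | 5.60 | 5.60 | 1.000 | 5.0% | 5.2% |
| 19/19/19 | 0.3/0.3/0.6 | 6.63 | 6.14 | 0.926 | 7.0% | 7.5% |
| 19/19/19 | 0.3/0.2/0.6 | 7.09 | 6.31 | 0.890 | 8.1% | 8.1% |
| 15/19/22 | 0.3/0.2/0.6 | 7.08 | 6.22 | 0.878 | 8.5% | 9.0% |
| 19/22/19 | 0.3/0.3/0.6 | 6.63 | 6.47 | 0.976 | 5.6% | not run |
| 19/24/19 | 0.3/0.3/0.6 | 6.63 | 6.72 | 1.014 | 4.7% | not run |
| 19/24/19 | 0.3/0.3/0.5 | 6.63 | 6.92 | 1.043 | 4.1% | 4.6% |
| 19/24/15 | 0.3/0.3/0.5 | 6.01 | 6.64 | 1.105 | 3.0% | 3.4% |

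**Grid.** Correlations were varied from 0.1 to 0.7 with r(3,12) ≥ r(0,3) ≥ r(0,12). The ratio runs from 0.75 to 1.00 with equal SDs. With each SD taken from 15, 19 or 23 it runs from 0.72 to 1.29, and about 85% of cells lie below 1. The cells are unweighted, so that share is not a probability.

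**With dropout.** Two separate REML simulations used 28 per arm, 6 lost per arm at 12 months, SD 19 and correlations 0.3/0.2/0.6. One (3,000 replicates) gave true SE 6.8, model SE 6.2 and type I error 7.8%; the other (2,000 replicates) gave 7.0, 6.2 and 9.2%.

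**Plain 12-month difference.** With complete data the model variance is (2/n) × mean of the three variances, and the true variance is (2/n) × SD12². With equal SDs these coincide whatever the correlations.

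**The case against.** The strongest objection concerns direction. A reader might infer that the primary interval is too narrow and that the type I error exceeds 5%. The document does not support that, because it gives neither correlations nor SDs by visit. Even when the two post-operative scores correlate most strongly with each other, a clearly larger 3-month SD brings the ratio to 1 or above. This objection stands, and the point is stated accordingly.

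Second, the endpoint is pain at 12 months, and the sample size compares the groups there. For that contrast, with equal SDs and complete data, the random-intercept standard error is correct. This also stands. But the analysis sentence describes differences from baseline to each follow-up, and for that contrast the problem is real.

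Third, a journal article condenses. It does not exclude a richer residual structure beside the person effect, and an analysis plan that is not shown may specify one. This stands in part. The article does fix the random part, however, and reserves the robust variance for binary outcomes. Diagnostic plots can reveal unequal spread by visit, but no fallback is stated.

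Fourth, the effect is modest. In the first dropout simulation the 95% half-width is short by about 1.96 × (6.8 − 6.2) = 1.2 mm against a target of 18 mm. With complete data the point estimate is unchanged. Both are correct, and they limit the weight of the point without removing it.

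**Conclusion.** The point holds in a conditional form. As written, and with default residuals, the primary model can misstate the standard error of the baseline-to-12-month group contrast in either direction. Understatement is the more plausible direction if SDs are similar across visits and the 0-to-12-month correlation is the lowest: a ratio of about 0.89 and a type I error of about 8% under the assumed 0.3/0.2/0.6. If the 3-month SD is clearly the largest or the 12-month SD the smallest, the standard error is about right or too large, with a type I error of about 3-5%. Across the tabulated scenarios the ratio runs from 0.88 to 1.10.

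All of this rests on assumed SDs and correlations, on a change-from-baseline contrast and on ordinary residuals. It is not evidence that the interval will be too narrow, and it does not bear on the 23 or 28 patients per arm.

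**What to change.** Before the data are seen, specify the primary model with time as three categories and an unstructured residual covariance over baseline, 3 and 12 months, fitted by REML, in place of the random intercept alone. Add a small-sample degrees-of-freedom correction (Kenward-Roger or Satterthwaite) if the chosen software version offers it, since only about 44 to 56 patients contribute. State the fallback: if the model does not converge, keep the random intercept with standard errors that are cluster-robust by person. In the same sentence, say whether the primary result is the change contrast or the 12-month difference.

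The cost is a change of wording, six covariance parameters instead of two, and possibly a slightly wider interval. The sample size stays as stated.

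### The planned multiple imputation assumes missing at random, as the mixed model does, so it cannot serve as the check for informative missingness that the protocol says it is

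*Protocol article*

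**What the plan says.** All the relevant text is in the protocol article, section Sample size and statistical analysis.

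- Primary model: a "mixed effects linear regression model with a random person level and systematic effects of time, group and the interaction between time and group".
- Analysis set: "The primary analysis will use the intention-to treat principle including all randomised participants".
- Purpose of the imputation: "We will employ multiple imputation methods in order to assess the sensitivity of the mixed model to any informative missing values".
- Inputs to the imputation: "Imputations will be performed using baseline characteristics and non-missing pain measurements on individual levels".
- Loss to follow-up: about 20% at one year is allowed for in the sample size.
- Retention: "Patients who discontinue the intervention will be encouraged to participate in the follow up test anyway". Those who agree are analysed in their original group.

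The section also says that data from patients who withdraw will be looked at, without saying how. The article mentions no shift parameter, pattern-mixture model, selection model, reference-based imputation or tipping-point analysis.

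**The concern.** Missingness is informative when, given everything observed, the missing 12-month pain scores differ systematically from the scores that were seen. An imputation that draws missing values from their relation to observed baseline characteristics and observed pain scores sets that difference to zero. A mixed model fitted by likelihood to the available measurements does the same. The stated purpose and the stated method therefore do not match.

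Informative loss is plausible in this trial. Patients are not blinded (text below Fig. 2) and report the primary outcome themselves (Table 2). Only the education arm has seven sessions to give up (Intervention group), and follow-up after giving them up depends on the patient's agreement. If dropouts in that arm had more pain than their observed data predict, both analyses would overstate the benefit by a similar amount. A reader shown that they agree could then take the result as robust to a mechanism that neither analysis examined.

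**Working it through.** **1. The plan's own figures.** Inputs: "Clinically important differences between the two groups is detected to be 18 mm"; "we assume a common standard deviation between participants of 19 mm on VAS"; alpha 0.05 (two-sided assumed); power 0.90.

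- n per arm = 2 × [19 × (1.960 + 1.282) / 18]² = 23.4. The plan states 23; rounding up gives 24.
- Allowance for loss: 23 × 1.20 = 27.6, so 28 per arm as stated. Dividing instead gives 23 / 0.80 = 28.75, so 29.

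The figures are reproduced to within a patient per arm, and this point does not turn on them. With 28 per arm and 20% loss, 28 × 0.80 = 22.4, so about 22 per arm are observed at 12 months.

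**2. What each analysis assumes.**

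| | Uses | Assumption about unseen 12-month VAS |
|---|---|---|
| Mixed model | Observed pain, time, group, time × group, person effect | As predicted by these (MAR) |
| Imputation as described | Observed pain plus baseline characteristics | As predicted by these (MAR, with a wider conditioning set) |
| Check for informative missingness | Either of the above plus a stated departure | Differs from the prediction by delta |

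The third row is the stated aim. The described method is the second.

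**3. Size of what goes unexamined.** If the missing patients in one arm differ from prediction by delta, then

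shift in group difference = missing fraction × delta.

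The deltas, and the 10% and 30% losses, are assumptions. The 20% loss is the protocol's allowance.

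| Loss | delta 5 mm | delta 10 mm | delta 18 mm |
|---|---|---|---|
| 10% | 0.5 | 1.0 | 1.8 |
| 20% | 1.0 | 2.0 | 3.6 |
| 30% | 1.5 | 3.0 | 5.4 |

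With the same loss and the same delta in both arms, 0.20 × delta − 0.20 × delta = 0.

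**4. Against the significance threshold.** For a simple comparison of 12-month means with 22 per arm, the smallest significant difference is

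t(0.975; 42 df) × 19 × √(2/22) = 2.018 × 19 × 0.3015 = 11.6 mm.

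- An observed 18 mm effect with an 18 mm one-arm departure becomes 18 − 3.6 = 14.4 mm, still above 11.6.
- Bringing 18 mm down to 11.6 mm needs delta = (18 − 11.6) / 0.20 = 32 mm.
- An observed 13 mm effect (chosen for illustration) becomes 13 − 2.0 = 11.0 mm at delta 10, below the threshold.

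This ignores the extra variance from imputation. The mixed model's own threshold will also differ somewhat.

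**5. Simulation.** Setting: 200 trials of 28 per arm, SD 19 mm, true 12-month difference −18 mm, about 20% missing, and imputation by arm from baseline and 3-month pain. The correlation between visits and the dropout mechanism are assumed. In the education arm, loss depends on 3-month pain (MAR) or on 12-month pain itself (not at random).

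| Correlation | Mechanism | Full data | Mixed model | Imputation |
|---|---|---|---|---|
| 0.3 | MAR | −17.5 | −17.7 | −17.9 |
| 0.5 | MAR | −17.7 | −17.7 | −17.7 |
| 0.3 | Not at random | −18.2 | −22.3 | −22.3 |
| 0.5 | Not at random | −17.8 | −20.8 | −21.0 |

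Under not-at-random loss, both methods overstate the benefit by about 3 to 4 mm, while their averages differ by only 0.0 to 0.2 mm. In single trials the two estimates differ with an SD of about 1.1 mm in these scenarios. That is noise and does not detect the mechanism.

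**The case against.** **A shift step may exist in an unseen analysis plan.** The article names the predictors for the imputation and does not rule out a later adjustment; a delta-adjusted analysis would use the same predictors. This is a fair reading of the article's silence. But the article gives a purpose and a method side by side, and the method given cannot serve the purpose. If a shift step exists, the text should say so.

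**The imputation is not redundant.** A reader might infer that it must reproduce the mixed model almost by construction. The documents do not support that: the imputation uses baseline characteristics that the mixed model leaves out, and the simulation above omitted that feature. A second simulation of 200 trials assumed pain correlation 0.4 and one baseline covariate correlated 0.5 with pain, with that covariate driving education-arm loss. It gave −19.0 for the mixed model, −17.9 for the imputation and −18.1 for full data, so the imputation removed about 1 mm of bias. This objection stands. The check has value, but for a wider form of MAR. When loss in that setting was not at random, both methods were again biased, by about 4 mm.

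**The protocol limits informative loss.** Stopping the education is kept separate from leaving follow-up, the VAS is collected by post or e-mail without needing a visit, and the last session is nine months before the primary endpoint. The 20% is a planning allowance, not a forecast of unequal loss. These points lower the likely size of the problem, but they do not turn the imputation into a test for it.

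**Conclusion.** The point holds at moderate severity. As described, the imputation is a MAR analysis with additional baseline covariates. It cannot assess dependence of missingness on the unobserved 12-month VAS, and its agreement with the mixed model would be no evidence of robustness to informative dropout.

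At 20% loss, the unexamined shift is 1.0 to 3.6 mm for assumed one-arm departures of 5 to 18 mm. That can decide a result near 11.6 mm. A reader might go further and infer that the trial's main conclusion is at risk whatever the result. The figures do not support that: an observed 18 mm effect would survive any departure up to about 32 mm in one arm, and balanced departures cancel. The primary model and its estimate are unaffected. The size rests on the protocol's SD and loss allowance, on the assumed deltas, and on a simple two-group comparison at 12 months.

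**What to change.** - Keep the mixed model as the primary analysis.
- Describe the present imputation as a MAR sensitivity analysis using additional baseline covariates, and drop the claim that it addresses informative missingness.
- Prespecify a delta-adjusted (pattern-mixture) imputation: impute by arm under MAR, then add a shift to the imputed 12-month VAS, first in the education arm alone and then in both arms. Increase the shift until the conclusion tips, and report the tipping point. A grid stopping at 20 mm would be too short for a result at the design effect, since 18 − 0.20 × 20 = 14 mm.
- Control-based imputation for education-arm dropouts is an optional addition.
- Fix the range and step of the shifts before the 12-month data are examined, since values chosen afterwards carry little weight.

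The cost is a change of wording, a few lines of code and a little more analysis; no new data are needed. The downside is that the robustness statement may be less favourable. If no such analysis is wanted, the stated purpose of the imputation should at least be corrected.
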